# Summary

**Introduction:** Malnutrition is a public health problem in Ethiopia. Malnutrition can affect children’s cognitive, behavioral and motor development. Further, healthy development and educational achievement can be compromised due to micronutrient deficiencies including iron deficiency. Different studies show that amaranth grain has better levels of macro and micronutrients especially iron to address the widespread malnutrition problem than other frequently used crops. This useful plant is widely grown in the research area, but it considered as a weed rather than a food crop by the community. Furthermore, adequate research has not been conducted in Ethiopia on amaranth’s potential to contribute in reducing the malnutrition problem. This research is initiated to look at amaranth and its potential in reducing iron deficiency anemia among children. The research will inform the public at large, policy makers and the academicians as it deals with an underutilized nutritious crop that has the potential to contribute to reduce the malnutrition problem in the country.

**Objective:** To assess the iron deficiency status of children and to evaluate the effect of an amaranth containing bread consumption on the anthropometry and iron deficiency status of children in the age of 24.0-59.9 months.

**Methodology:** A cross sectional study and a randomized controlled trial will be done. For the survey, random sampling will be used to select 340 children. Hemoglobin, serum ferritin, C- reactive protein and anthropometric measurements will be taken and used as the baseline data for the experimental study. In the randomized controlled trial, 100 children with hemoglobin level of less than 11 mg /dl and above 7 mg/dl (mild and moderate anemia) will be recruited into the trial after informed consent. Severely ill individuals will be referred to Hawassa Referal Hospital. Kebele-stratified simple random sampling will ensure 1:1 allocation to each group. Sequentially numbered, opaque, sealed envelopes will be used to assure concealment of allocation. The study subjects and parents (other caregivers in the absence of parents) will be kept uniformed about the trial allocation. Statistical analysis will be done using the latest SPSS version and ENA for SMART software. The survey will present descriptive statistics including frequencies, means, ranges and demographic characteristics of the population. The trial will be analyzed according to the intention-to-treat principles using logistic crude and site adjusted regression models with a mean difference in Hemoglobin as the primary outcome measure.

**Conclusion:** This research project has the potential to be hypothesis generating and will inform policy makers and scientists about amaranth’s potential to combat malnutrition specifically iron deficiency in the area.

# Acronyms

| BC | Beta-Carotene |
| --- | --- |
| CRP | C – Reactive Protein |
| EPHI | Ethiopian Public Health Institute |
| FE MNP | Ferro Magnetic Nano particles |
| FGD | Focus Group Discussion |
| FVS | Food Varity Scores |
| HDD | House Hold Dietary Diversity |
| HAZ | Height For Age Z-Score |
| IDA | Iron Deficiency Anemia |
| IDD | Individual Dietary Diversity |
| IYCF | Infant Yange Child Feeding |
| MND | Micro Nutrient Deficiency |
| MUAC | Mid Upper Arm Circumference |
| PLWHA | People Living With HIV/AIDS |
| RDA | Recommended Dietary Intake |
| RES | Reticule Endothelial System |
| SRL | Sustainable Rural Livelihoods |
| WHO | World Health Organization |

# 1. Introduction

## 1.1. Background

Ethiopia is one of the developing countries in the world where children and their mothers suffer most from poor health and nutrition. Malnutrition is the leading cause of death among children aged under 5 years in Ethiopia ([1](#_ENREF_1)). The country is challenged with the highest rates of stunting and underweight in the world. The recent Ethiopian Demographic Health Survey ([2](#_ENREF_2)) reported that almost half (44%) of Ethiopian children under five years of age were stunted (an indication of chronic malnutrition) and close to one in four (21%) were severely stunted. 10% of children under five years are wasted (an indication of acute malnutrition) which is considered a high prevalence according to WHO’s classification system ([3](#_ENREF_3)).

Micronutrient deficiency is a major contributor to childhood morbidity and mortality in Ethiopia. Iron, Iodine, vitamin A and zinc are recognized as ‘‘problem nutrients’’. Anemia is one of the major public health problems in Ethiopia. According to available information it is indicated that about 44% of children under five years are anemic in Ethiopia ([4](#_ENREF_4), [5](#_ENREF_5)). The World Health Organization (WHO) considers anemia prevalence over 40 percent in a population to be a major public health problem. Low iron intake in children is associated with increased morbidity and mortality as well as limited physical and cognitive development. IDA can result in compromised cognitive, behavioral and motor development as well as sub-optimal educational achievement ([6](#_ENREF_6), [7](#_ENREF_7)). Inadequate iron intake is responsible for more than half of anemia cases as diets consisting of mostly staple food dominated by starchy cereals are common for most of the poor people in Ethiopia. The diets are typically low in lipids, protein, vitamins and minerals ([2](#_ENREF_2), [6](#_ENREF_6)).

Iron is one of essential micronutrient required largely for children aged 2 to 5 years of age. An intake of 7-10 mg of iron is the recommended daily intake, children should consume via iron-rich foods. The available data in Ethiopia indicates that the majority of children are not consuming iron-rich foods. Only 5 percent of children consume meat, fish or poultry, which are bio-available, iron rich foods ([2](#_ENREF_2)). A study among school-aged children from west Ethiopia found an anemia prevalence of out 43.7% of which 37.4% was Iron Deficiency Anemia (IDA) which was associated with not-consuming protein source foods, dairy products, and discretionary calories ([5](#_ENREF_5)). The other predictors of IDA were not-consuming dairy products, not-consuming discretionary calories, low family income and parasitic infections ([5](#_ENREF_5)).

There are different methods to solve the problem of iron deficiency such as food fortification and supplementation. Iron supplementation of pregnant women, which address a limited number of women is the only IDA intervention currently implemented in Ethiopia including the research area to combat iron deficiency anemia. An increasing number of studies reported that iron supplementation intervention increases morbidity and causes unfavorable shifts in the gut microbial composition along with an increase in intestinal inflammation, particularly in children with a high infectious disease burden ([8](#_ENREF_8)). Additionally, food fortification and supplementation is expensive and cannot be afforded by the majority of the poor Ethiopian population. Supplementation has so far not shown to be a sustainable solution to prevent iron deficiency at group level. Amaranth contains protein and micronutrient of unusually higher amount than staple cereals ([9](#_ENREF_9)). Amaranth grain contains twice the level of calcium than in milk, five times the level of iron in wheat, higher potassium, phosphorous and vitamins A, E and folic acid than cereal grains. It can be cultivated for both its seeds, which are used as a grain and its leaves which are used as vegetables ([9](#_ENREF_9), [10](#_ENREF_10)).

Even though amaranth contains quality amino-acids, high iron and other micro-nutrients, it also has a high concentration of phytic acid that can reduce the bio-availability of iron. A recent study from Kenya ([10](#_ENREF_10)) indicated that amaranth has no effect on the iron status of children due to high phytate to iron ratio. However, research conducted in Ethiopia and Kenya showed that homemade processing such as soaking and germination of the grain amaranth could reduce phytate to an acceptable phytate to iron ratio level that can contribute to increased bio-availability of iron ([11](#_ENREF_11), [12](#_ENREF_12)).

Amaranth is producing cereal like gluten-free seeds, which has an outstanding agronomic performance owing to its resistance to drought, hot climate and pests. It can grow in all-weather conditions specially the place where maize can grow. It also gives higher yields than maize. It doesn’t require high nitrogen like maize but responds well to fertilization. Amaranth produce a large amount of biomass in a short period of time and therefore has the potential to contribute a substantial increase in world food production grain yields ([13](#_ENREF_13)).

## Statement of the problem

Anemia is a global health problem. Iron deficiency is the most common micronutrient deficiency (MND) worldwide and most common in developing countries which lead to microcytic anemia. Anemia is a major public health problem in Ethiopia and it is more common among groups with low socio economic status ([6](#_ENREF_6), [14](#_ENREF_14)).The major cause for IDA is insufficient dietary iron intake, compounded by high incidence of malaria and other parasitic diseases. Ethiopian diet is mainly composed of cereals (maize, sorghum), tubers and root crops (ensete, potatoes, and sweet potatoes) which are low in iron and other micronutrients([15](#_ENREF_15)). Despite a large livestock population, the food supply of animal products such as meat is very limited and consumption of these products is especially low in rural areas because it is expensive. Thus, there is a need to find other sustainable contributors to the diet that can improve the nutritional status of children. Therefore, this study aims to evaluate the effect of processed amaranth grain recipes consumption to reduce iron deficiency anemia and improve anthropometric status among children in southern Ethiopia.

## Study justification

The grain amaranth has the better level of nutrients and it could be a better choice to use for food formulation ([16](#_ENREF_16), [17](#_ENREF_17)) at the household level and at factories than maize. Amaranth is draught resistant, can be grown in almost all parts of the country and has the ability to give more yield than maize and other staple crops in the area. So amaranth is one alternative to address the widespread protein and micronutrient deficiencies with low cost ([18](#_ENREF_18)).

Even though this prospective crop is widely grown in Ethiopia, it is not used as a food and food supplement; rather it is considered a useless weed. Therefore, this research will create new insight in amaranth’s ability to reduce malnutrition, specifically iron deficiency anemia. It also tests out a low cost iron rich recipe relevant for the Ethiopian society that cannot afford fortified foods or animal products.

# Aim

To reduce iron deficiency anemia in children 24.0 up to 59.9 months of age by using amaranth grain in southern Ethiopia.

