## **2.1. Research questions**:

1. What is the prevalence of iron deficiency anemia defined as Hemoglobin below 11mg/dl and serum ferritin below 12µg/L among children from 24.0 to 59.9 months of age in southern Ethiopia?
2. Does consumption of 150 mg bread daily containing 70 mass percentage amaranth grain increases mean hemoglobin level by 0.7mg/dl among children 24.0-59.9 months of age compared to equivalent amount of 100 percent maize bread in southern Ethiopia?
3. Is Amaranth grain culturally acceptable and how is the policy direction towards amaranth grain to use as staple food in Ethiopia?

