# PICO

P- Children aged 24.0 -59.9 months in southern Ethiopia, Tulla sub city, with mild and moderate anemia

I - Daily feeding of 150g bread containing 70 mass % amaranth grain and 30 mass % mashed chickpea

C -Daily feeding of 150g bread containing 100% maize

O- Change in hemoglobin level, change in ferritin status, changes in anthropometric status.

The research questions will be answered in three subsequent papers and the general and specific objectives are given below for the three papers.

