# Study variables

The primary outcome measure of this study will is hemoglobin of children and serum ferritin. The secondary outcomes are anthropometry measures (height/length, weight and mid-upper-arm circumference) (anthropometric z- scores will be derived based on WHO growth standards 2006 (give reference)), conjunctiva pallor and child morbidity pattern including hospitalization, diarrhea, cough and fever (type, frequency, duration and symptoms of illnesses). Potential effect modifiers and confounders will be captured to describe the population and look at the successfulness of randomization (sex, education level, occupation and income), dietary practices (number of meals and frequency of food consumption) including use of amaranth in the diet and type of staple foods.

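### The Aim and one trial objective concern iron deficiency anemia, but no listed trial outcome classifies a child as anemic or iron deficient anemic at the end of feeding

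*Protocol*

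**What the plan says.** - **Target condition.** The Aim is "To reduce iron deficiency anemia in children 24.0 up to 59.9 months of age". The Summary says the study will "evaluate the effect of an amaranth containing bread consumption on the anthropometry and iron deficiency status of children". Under General objective two, the fifth specific objective compares cost-effectiveness in preventing iron deficiency anemia.
- **Definition.** The condition is defined once, in Research questions (2.1), for the survey prevalence question: "iron deficiency anemia defined as Hemoglobin below 11mg/dl and serum ferritin below 12µg/L".
- **Trial outcomes.** Study variables states: "The primary outcome measure of this study will is hemoglobin of children and serum ferritin". The secondary outcomes are anthropometry and "conjunctiva pallor and child morbidity pattern including hospitalization, diarrhea, cough and fever". PICO lists "Change in hemoglobin level, change in ferritin status, changes in anthropometric status", with no definition of ferritin status. The first two specific objectives of the trial compare hemoglobin and ferritin values.
- **Trial hypothesis and size.** The hypothesis (2.2), General objective two and Sample Size all rest on a 0.7 difference in mean hemoglobin. Sample Size gives SD 1, 90% power, 12% attrition and a total of 99, rounded to 100.
- **Analysis.** The Summary and Statistical methods both prescribe logistic regression for hemoglobin, and the Summary names a mean difference as the primary measure. Neither defines a binary event.
- **Schedule.** Table 4 places hemoglobin, ferritin and CRP in Month 2 and again in Month 8, the last month of feeding.

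**The concern.** What the trial is said to be for and what it lists as outcomes do not match. Iron deficiency anemia is a joint condition within a child: low hemoglobin and low ferritin together. Two separate group means cannot give the number of children who have it. Every child also enters below 11 g/dl (Inclusion criteria), so how many are no longer anemic after six months is a natural reading of the Aim, and no listed outcome gives it.

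The fifth objective depends directly on the missing outcome, because cost-effectiveness in preventing a condition needs a measure of that condition by arm. The undefined ferritin status in PICO and the logistic model for hemoglobin suggest that a classified outcome may have been intended but was never fixed.

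If the protocol is followed as written, a favourable mean difference could be reported as a reduction in iron deficiency anemia without any planned comparison of it. Alternatively the comparison could be built after the data are seen, with cut-offs, time point and handling of inflammation open to choice.

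**Working it through.** **1. What the sample size supports.** Inputs from Sample Size: difference 0.7, SD 1, power 90%, attrition 12%. Alpha is not stated; 0.05 two-sided is assumed.

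- Normal formula: n per arm = 2 × ((1.960 + 1.282) / 0.7)² = 42.9, so 43. The total is 86, and 86 / 0.88 = 97.7, so 98.
- t-test version: 43.9, so 44 per arm. The total is 88; 88 / 0.88 = 100, or 88 × 1.12 = 98.6, so 99.

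The stated 99 (100) reproduces. The trial is sized for a mean, with about 50 × 0.88 = 44 children analysed per arm.

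**2. Outcomes set against the Aim.**

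| Place | What is compared | Anemia or iron deficiency anemia at end, by arm? |
|---|---|---|
| PICO | Change in hemoglobin, ferritin status, anthropometric status | No; status undefined |
| General objective two, objectives 1 to 3 | Hemoglobin and ferritin values, anthropometry | No |
| General objective two, objective 5 | Cost-effectiveness in preventing iron deficiency anemia | Requires it; no outcome supplies it |
| Study variables | Hemoglobin, ferritin, anthropometry, pallor, morbidity | No; pallor is a clinical sign |
| Research questions, question 1 | Prevalence by the two cut-offs | Survey only |

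**3. What a 0.7 difference implies for anemia.** End-of-study hemoglobin is assumed normal with the protocol's SD of 1. The maize-arm end mean m is not in the documents and is varied from 9.5 to 11.0 g/dl.

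- Maize: p₀ = Φ(11 − m). Amaranth: p₁ = Φ(11 − m − 0.7).
- Unadjusted 95% half-width = 1.96 × √{[p₀(1 − p₀) + p₁(1 − p₁)] / 44}.

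| m (g/dl) | Maize anemic | Amaranth anemic | Difference (points) | Half-width (points) |
|---|---|---|---|---|
| 9.5 | 93.3% | 78.8% | 14.5 | 14.1 |
| 10.0 | 84.1% | 61.8% | 22.3 | 18.0 |
| 10.5 | 69.1% | 42.1% | 27.1 | 20.0 |
| 11.0 | 50.0% | 24.2% | 25.8 | 19.5 |

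For m = 10.5, as an example: √[(0.2133 + 0.2437) / 44] = 0.1019, and × 1.96 = 0.200.

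The same mean shift thus corresponds to falls that differ almost twofold. Power for the binary anemia comparison at 44 per arm is about 50% to 74% over this range.

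**4. Iron deficiency anemia.** This needs a further assumption: the share of anemic children who are iron deficient. With half to three quarters, equal in both arms, the fall is about 7 to 21 points, the half-width 16 to 21 points, and the power about 10% to 54%. An equal share leaves out any effect of the bread on iron deficiency among children who remain anemic, so this is an illustration of precision and not a forecast.

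**The case against.** The strongest reply is that the Aim is one line heading a project of three papers, while the trial's own question is consistent throughout: a 0.7 difference in mean hemoglobin in research question 2, the hypothesis, General objective two and Sample Size. Continuous biomarkers are a legitimate way to study an effect on a condition. Ferritin is named as a primary outcome, which bears on iron status. Derived classifications are often left to an analysis plan, which is not shown. The percentages above also rest on assumed control means.

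Much of this stands. Mean hemoglobin is a sound primary outcome and nothing here argues for replacing it. The percentages show that a mean does not determine a prevalence; they do not predict the result.

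A reader might also infer that the trial cannot tell whether iron deficiency anemia was reduced. The documents do not support that. Hemoglobin, ferritin and CRP are all scheduled in Month 8, and the cut-offs are in the Research questions, so the classification can be derived. What is lacking is pre-specification, not data.

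The appeal to an analysis plan does not dispose of the point. Aim, objectives and outcome list are protocol content, and here the fifth objective calls for something the outcome list does not contain.

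**Conclusion.** The point holds as a mismatch within the protocol. The Aim and the fifth trial objective concern iron deficiency anemia, and no listed trial outcome classifies children for it, or for anemia, at the end of feeding. A statement that the condition was reduced would have no planned comparison behind it and would be post hoc.

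The consequence is moderate: the primary comparison of mean hemoglobin and its sample size are unaffected. That the mean cannot stand in for the prevalence is shown by a fall in anemia of about 15 to 27 points for the same 0.7 difference. This rests on normality and SD 1 at the end of the study, and on maize-arm means of 9.5 to 11.0 g/dl that the documents do not give. That the classification is absent rests on no assumption.

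**What to change.** In Study variables, add two secondary trial outcomes at Month 8, compared by randomised arm:

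- (a) anemia, hemoglobin below 11 g/dl;
- (b) iron deficiency anemia by the definition in Research questions (2.1).

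Report each as a risk difference with 95% confidence interval, adjusted for kebele and continuous baseline hemoglobin, and for baseline ferritin as well in (b). Baseline anemia as a yes/no variable is constant by the entry criterion and cannot serve. Use CRP in a pre-specified sensitivity analysis of (b), because ferritin rises with inflammation.

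Use (b) as the effect measure for the fifth objective and as the basis for any statement about iron deficiency anemia, presented as an estimate with its interval.

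Keep mean hemoglobin as primary and analyse it with a linear model. In the Summary and Statistical methods, restrict logistic regression to the binary outcomes; adjusted risk differences can be obtained from it by averaging predicted risks over the trial children.

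The cost is wording only: no new blood sample, and no change to the primary outcome or sample size. The downside is imprecision. With 44 per arm the unadjusted half-width for anemia is roughly 14 to 20 points under the assumed control means, and an inconclusive result for (b) is quite possible.

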## **2.1. Research questions**:

1. What is the prevalence of iron deficiency anemia defined as Hemoglobin below 11mg/dl and serum ferritin below 12µg/L among children from 24.0 to 59.9 months of age in southern Ethiopia?
2. Does consumption of 150 mg bread daily containing 70 mass percentage amaranth grain increases mean hemoglobin level by 0.7mg/dl among children 24.0-59.9 months of age compared to equivalent amount of 100 percent maize bread in southern Ethiopia?
3. Is Amaranth grain culturally acceptable and how is the policy direction towards amaranth grain to use as staple food in Ethiopia?

## 2.2. Hypothesis of this study

**HO:** Feeding 150gm of bread containing 70 mass percentage amaranth grain and 30 mass percentage chickpea per day for mild and moderate anemic children 24.0 up to 59.9 months of age for 6 months will not increase the mean hemoglobin level by 0.7g/dl compared to 150gm of 100 percent Maize containing bread in Tulla sub city southern Ethiopia.

**HA**: Feeding 150gm of bread containing 70 mass percentage amaranth grain and 30 mass percentage chickpea per day for mild and moderate anemic children 24.0 up to 59.9 months of age for 6 month will increase the mean hemoglobin level by 0.7g/dl compared to 150gm of 100 percent maize bread in Tula sub city ,southern Ethiopia.

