## General objective two

To evaluate if feeding children with either 150gm bread containing 70mass% amaranth grain and 30mass% chickpea per day for 6 month will increase the hemoglobin level of mild and moderate anemic children 24.0 up to59.9 months of age by 0.7g/dl compared with children in equivalent amount of 100% maize bread in Tulla sub city south Ethiopia .

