**Specific objective**

1. To compare the hemoglobin values in children receiving amaranth grain containing bread and children receiving maize bread in Tulla sub city South Ethiopia.
2. To compare the ferritin values in children receiving amaranth grain containing bread with children receiving maize bread in Tulla sub city south Ethiopia.
3. To compare the anthropometry indices in children receiving amaranth grain containing bread with children receiving maize bread in Tulla sub city south Ethiopia.
4. To compare incidence of childhood illness in children receiving amaranth grain containing bread with children maize bread in Tulla sub city south Ethiopia.
5. To compare cost effectiveness of amaranth containing bread on the prevention of iron deficiency anemia in Tulla sub city south Ethiopia
6. To compare compliance and adherence of mother between amaranth containing bread and maize bread groups.

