## Sample Size

The base line data (survey part) will be used as a basis for the trial part. After completing the survey part the trial sample will be recruited from the survey study participants, in this way the survey will be providing the baseline data for the trial. The survey sample size will be 340 considering a need for 100 trial participants, 33% of mild and moderate anemia prevalence in south Ethiopia, 0.5 degree of precision and 95% confidence intervals. The survey sample size may be increased till the numbers of eligible individuals are identified for the trial if anemia is less prevalent than 33%.

The sample size of the trial is calculated by using Stata I.C. 14 software using the sample size command, considering 0.7 mean difference,1 standard deviation, power 90% and attrition rate 12% the total sample size will be 99 (100) in the two groups. The total sample will be divided in to the amarnth70%/chickpea30% versus the maize 100% groups. Thus it will be 50 in the amaranth/chickpea group and 50 in the maize group ([2](#_ENREF_2)).

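### The hypotheses carry 0.7 g/dl as their content, but the sample size and its 90% power belong to a test of zero difference

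*Protocol*

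**What the plan says.** Section 2.2 of the protocol holds its only formal hypotheses. Under H0, six months of the amaranth and chickpea bread "will not increase the mean hemoglobin level by 0.7g/dl compared to 150gm of 100 percent Maize containing bread". Under HA it "will increase the mean hemoglobin level by 0.7g/dl compared to 150gm of 100 percent maize bread". General objective two asks whether the bread "will increase the hemoglobin level of mild and moderate anemic children 24.0 up to59.9 months of age by 0.7g/dl" relative to maize bread, and research question 2 (section 2.1) asks the same with 0.7, there printed in mg/dl.

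The Sample Size section assumes "0.7 mean difference,1 standard deviation", with 90% power and 12% attrition, and arrives at 99, rounded to 100, or 50 per arm. It gives no null value, alpha or sidedness for the trial. The 95% confidence mentioned in that section belongs to the survey.

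Specific objective 1 under General objective two has no threshold: "To compare the hemoglobin values in children receiving amaranth grain containing bread and children receiving maize bread". The Summary names a mean difference in hemoglobin as the primary outcome measure. The Statistical methods section plans an intention-to-treat analysis of hemoglobin. Neither mentions a test against 0.7.

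**The concern.** One number has two roles that exclude each other. In a superiority test against zero, 0.7 is the value of the alternative at which power is calculated, and the null value is zero. In section 2.2, 0.7 is what H0 denies and HA asserts, so the natural testable form of H0 is a difference of at most 0.7. A trial cannot have 90% power at a true difference that its own null hypothesis contains.

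What is at stake is how the result on a primary outcome is read. Suppose the observed difference is 0.55 g/dl and its confidence interval excludes zero. A reader who follows the sample size calls this a positive trial. A reader who follows section 2.2 can say that HA was not met. The protocol does not settle which reading applies, so the choice could be made after the data are seen.

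**Working it through.** **Inputs.** Difference 0.7, SD 1, power 90%, attrition 12%, total 99 (100), allocation 1:1, all from Sample Size. The unit g/dl comes from section 2.2. Alpha is not stated for the trial; two-sided 5% is assumed and then tested against the stated total.

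**1. Reproducing the stated size with a null of zero.**
- Two-sample t test, two-sided 5%: 43 per arm gives 89.4% power and 44 per arm gives 90.1%, so 44 per arm and 88 in all.
- Attrition: 88 × 1.12 = 98.6, which is the stated 99; 88 / 0.88 = 100, which is the stated rounded figure.
- The normal approximation gives 43 per arm and 86 in all, or 97 to 98 after attrition, which is close.
- One-sided 2.5% has the same critical value in the direction of benefit, so the same size.
- One-sided 5% needs 36 per arm by the t test: 72 × 1.12 = 80.6 or 72 / 0.88 = 81.8. This does not match.

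The stated total is therefore that of a test of zero difference with 0.7 as the assumed true effect.

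**2. Reading A: 0.7 is a threshold to be shown (H0: difference ≤ 0.7).**
- SE = SD × √(2/n) = √(2/44) = 0.213.
- Probability of rejection = Φ((δ − 0.7)/SE − 1.96), where δ is the true difference.
- At δ = 0.7 the first term is zero for every n, leaving Φ(−1.96) = 2.5%. This is the type I error at the boundary of the null. With a one-sided alpha of 5% it would be 5%.
- With 44 per arm the probability is 6.8% at δ = 0.8, 29% at 1.0 and 65% at 1.2.
- For 90% power, δ = 0.7 + (1.960 + 1.282) × 0.213 = 1.39 g/dl. With all 50 per arm, SE = 0.2 and δ = 1.35 g/dl.

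**3. Reading B: 0.7 is a target for the point estimate.**
- Zero is rejected when the observed difference exceeds 1.988 × 0.213 = 0.424 (t critical value, 86 degrees of freedom).
- If the true difference is 0.7, P(0.424 < observed < 0.7) = 0.5 − Φ((0.424 − 0.7)/0.213) = 0.5 − 0.098 = 0.40.
- With all 50 per arm the lower edge falls to 0.39 and the probability is about 44%.

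Readings A and B are different rules and their figures must not be combined. The protocol states neither rule.

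**The case against.** The strongest reply is that section 2.2 is loose wording and nothing more. It says by 0.7, not by more than or at least 0.7, and the anticipated effect may simply have been carried from the sample size into the hypothesis sentence. Specific objective 1, the Summary and the Statistical methods section all describe an ordinary comparison of the arms. On that view the trial has its stated 90% power and its size is right. This stands, and it limits the point to the wording. It does not remove the point, because section 2.2 is the only formal hypothesis, two other sections repeat its 0.7, and nothing in the protocol says that the null value is zero.

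Two stronger readings are tempting, and the document does not support them.

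- A reader might infer that the trial has 2.5% power instead of 90%. The 2.5% is the type I error at the boundary of one reading of H0. It is the same at every sample size, so it says nothing about the adequacy of 100 children. It also presupposes a rule, that the lower confidence limit must exceed 0.7, which appears nowhere in the protocol.
- A reader might infer that a directional HA contradicts the sample size. It does not: one-sided 2.5% gives the same number as two-sided 5%. Only one-sided 5% is ruled out. What is missing is a statement of which applies.

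A statistical analysis plan may state the test. If it tests zero difference, it will still disagree with H0 as the protocol words it.

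**Conclusion.** The point holds as an error in the stated hypotheses, not in the number of children. The 90% power belongs to a null of zero, whereas section 2.2, research question 2 and General objective two make 0.7 g/dl the content of the hypothesis. Taken as a threshold, a true effect of 0.7 is declared a success only at the type I error rate, and about 1.39 g/dl would be needed for 90% power with 44 per arm. Taken as a point-estimate target, about 40% of trials with a true effect of 0.7 would reject zero and still fall short.

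These figures rest on SD 1, on 44 evaluable children per arm, and on an alpha of two-sided 5% (or one-sided 2.5%) inferred from reproducing the total. The mismatch itself needs no particular alpha: with a null of at most 0.7, a true effect of 0.7 lies inside the null at any significance level.

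**What to change.** - **Section 2.2:** state H0 as no difference in mean hemoglobin between the arms at 6 months, and HA as a difference.
- **Sample Size:** state alpha and sidedness (two-sided 5% matches the total), say that the null value is zero, and keep 0.7 g/dl only as the planning difference.
- **Research question 2 and General objective two:** reword them to ask whether mean hemoglobin differs between the arms, in line with specific objective 1. Bring the unit in research question 2 into line at the same time.
- **Reporting:** give the observed difference with its 95% confidence interval, and discuss 0.7 g/dl beside it without using it as a pass mark.

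The cost is a few sentences; the sample size does not change. If the sponsor does mean to show an increase of more than 0.7 g/dl, rewording is not enough. The size would then have to be recalculated with an assumed true effect above 0.7. For a true effect of 1.0, for example, 90% power needs 2 × (1.960 + 1.282)² / 0.3², or 234 per arm before attrition.
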